## Methods

### Study design

The therapeutic effect of Yokukansan for preoperative anxiety, its preventive effect on postoperative delirium, and its safety in cancer patients will be confirmed in a randomized, double-blind, placebo-controlled study. The investigators registered this study in the UMIN Clinical Trials Registry (UMIN-CTR) https://upload.umin.ac.jp/cgi-open-bin/ctr/ctr_view.cgi?recptno=R000031488 (UMIN000027561) prior to the start of the trial.

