### Safety outcomes

We define adverse reactions as any undesirable or unintended signs, symptoms, or diseases that occur from the day a study drug is administered through 5 days after surgery. We do not consider events to be adverse reactions if they are judged by the participating surgeons to be related to the surgery.

We describe the details of serious adverse events. The number of cases and the rate are calculated for each study group based on the CTCAE v 4.0. Regarding clinical laboratory values, we calculate summary statistics of changes from actual values and pre-dose values for each treatment group.

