### Sample size calculation

In this study, two primary endpoints are specified. If the superiority of Yokukansan over placebo for either endpoint is confirmed, the drug would be considered to be effective. Therefore, considering the Bonferroni adjustment for multiplicity, a two-sided significance level of 2.5% is used for each endpoint. Regarding the incidence of postoperative delirium—one of the primary endpoints—a previous meta-analysis reported that antipsychotics reduced the incidence of delirium by 50% compared to placebo [44]. The effect of Yokukansan against BPSD, which is thought to be a condition similar to delirium, has repeatedly been demonstrated in randomized controlled trials and is non-inferior to that of antipsychotics [27, 30–34], so we anticipated obtaining the same results against postoperative delirium. Therefore, we estimated an effect size for Yokukansan of 0.5 for postoperative delirium. Yokukansan has few side effects, and if we can show that its effects are comparable to those of antipsychotics, the results may change current clinical practice, in which antipsychotics are generally used as a first line pharmacotherapy to prevent postoperative delirium. Based on an observational study that we performed using exactly the same inclusion and exclusion criteria at the same hospital [5], we estimated the incidence of delirium at 40% in the placebo group and 20% in the Yokukansan group. Given a two-sided significance level of 2.5% and a statistical power of 80%, this indicates that 99 subjects per group are necessary. As for the change in preoperative anxiety, the minimum clinically meaningful difference in anxiety score was shown in a previous study to be 1.32 points, although in that case the subjects were patients with chronic obstructive lung disease [45]. Therefore, in this study we assume a between-group difference in the mean change in preoperative anxiety of 1.5 points. Assuming a 3-point standard deviation in the preoperative anxiety score, a two-sided significance level of 2.5%, and a statistical power of 80% based on the results of an observational study conducted at the National Cancer Center Hospital [13], 78 subjects per group are necessary. Considering the above and speculating that some subjects may later be found to be ineligible or may withdraw from the study, the planned number of registered subjects was determined to be 110 per group, or 220 in total.

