### Statistical analysis

The analysis sets for efficacy and safety include all registered subjects. The mean change in the HADS-A score before and after oral administration in each group, the point estimate of the between-group difference, and the 97.5% confidence interval are calculated. Group means are compared using the *t* test. The incidence of postoperative delirium in each group, the point estimate of the between-group difference, and the 97.5% confidence interval are calculated, and the proportions are compared by the chi-square test. Because there are two primary endpoints, Bonferroni adjustment for multiplicity is performed, and a two-sided significance level of 2.5% is used for the two comparisons. If superiority of the Yokukansan group is observed in either of the endpoints, treatment with Yokukansan will be considered to be useful. The interim analysis examined only the Yokukansan group but not both groups, and we do not regard this as a multiple analysis.

Interim analysis will be performed when the number of subjects who have completed the protocol treatment and are evaluable for both endpoints reaches one-third (*n* = 74) of 220, which is the target number of registered patients in this study. At that time, we will determine whether or not continuation of the study is appropriate. If it is determined that the main purpose of the study has not been fulfilled, the study will be discontinued, and the study results will be promptly disclosed. In principle, registration will not be suspended during the interim analysis. When the point estimate of the mean preoperative anxiety score in the Yokukansan group exceeds 5 points or the incidence of postoperative delirium exceeds 40% in the interim analysis, the Independent Data Monitoring Committee, which consists of three external members, will judge whether or not to discontinue the study.

Serious adverse events are described in detail. For other adverse events, the number of subjects with the highest observed grade and the incidence of the highest grade in each treatment group are calculated, and the groups are compared by the Mantel test.

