We define the analysis sets as follows. The *full analysis set* consists of all randomized subjects who satisfy eligibility criteria, receive any study drug, participate in at least one postbaseline assessment, and have no Good Clinical Practice (GCP) violations. The *per-protocol set* excludes subjects in which the study is not carried out as per protocol because consent is withdrawn, whose surgery is canceled, who do not take the study drug according to the protocol, etc. The *safety analysis set* includes all subjects who receive any study treatment (including control) but excludes subjects who withdraw prior to receiving any treatment. Data that have been rejected due to missing information, lack of clarity, or faulty handling of data are not included in the analysis. We do not impute the missing data.

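### The one named between-arm safety test covers only adverse events other than serious ones, so each subject's highest grade omits serious events (minor)

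*Protocol article*

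**What the plan says.** All references are to the protocol article.

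- **Study design** makes safety an aim of the randomised comparison: "its safety in cancer patients will be confirmed in a randomized, double-blind, placebo-controlled study". The last paragraph of Background also lists safety in the objective.
- **Safety outcomes** says "We describe the details of serious adverse events", and the next sentence adds "The number of cases and the rate are calculated for each study group based on the CTCAE v 4.0". That second sentence is not restricted to non-serious events.
- **Statistical analysis** splits adverse events in two. On the first part: "Serious adverse events are described in detail". On the rest: "For other adverse events, the number of subjects with the highest observed grade and the incidence of the highest grade in each treatment group are" to be tabulated. The same sentence attaches the between-arm test to that table: "and the groups are compared by the Mantel test".
- The safety analysis set "includes all subjects who receive any study treatment (including control) but excludes subjects who withdraw prior to receiving any treatment".

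The article names no other between-arm safety test. It gives no significance level for the Mantel test; the 2.5% level is tied to the two efficacy endpoints.

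**The concern.** The word *other* comes directly after the sentence on serious events, so its plain meaning is non-serious. Two consequences follow.

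First, the quantity tested is not a subject's highest grade. If one overall worst grade is taken per subject, a subject whose worst event was serious is graded on a lesser event, or as having none. If the worst grade is taken for each event type, serious occurrences still drop out of the table.

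Second, the null hypothesis becomes equality of non-serious grades between the arms. That is only part of the safety question, and it omits the events a reader would most want compared with placebo. Seriousness and CTCAE grade are different attributes, so selecting events on one before analysing the other truncates the grade distribution.

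This is a scope rule that the article states, not a detail it leaves to another document. At stake is the usefulness of the only formal comparison attached to a stated objective.

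**Working it through.** **1. The plan's own figures.** No figure is given for the safety comparison. The arm size comes from the efficacy calculation: "the planned number of registered subjects was determined to be 110 per group, or 220 in total". The delirium requirement behind it reproduces. With z = 2.2414 (two-sided 2.5%) and 0.8416 (80% power), (2.2414·√(2·0.3·0.7) + 0.8416·√(0.4·0.6 + 0.2·0.8))² / 0.2² = 98.5, that is 99 per group as stated. The anxiety requirement gives 77 by normal approximation against the stated 78. Neither bears on safety.

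**2. What the test as written can see.** Suppose non-serious grades have the same distribution in both arms and only serious events differ. The Mantel statistic is (N − 1)r², where r is the correlation between arm and grade. If serious events are not in the grade, r does not depend on them, and the test rejects at its nominal level however large the excess. This follows from the scope and needs no assumed rate. In simulation it rejected in 5.05–5.15% of trials, counting both directions at two-sided 5%.

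**3. What including serious events would add.** The inputs are assumptions, because the article gives neither serious-event rates nor a grade distribution: n = 110 per arm, two-sided 5%, and serious events of grade 3 or 4.

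- Distribution A: highest non-serious grade 0/1/2/3 in 60/25/12/3%.
- Distribution B: the same grades in 50/30/15/5%, with serious events 70% grade 3 and 30% grade 4.

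Hand check for B at 5% versus 15%:

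- Mean non-serious grade = 0.30 + 2·0.15 + 3·0.05 = 0.75. Mean serious grade = 3·0.7 + 4·0.3 = 3.3.
- Arm means: 0.95·0.75 + 0.05·3.3 = 0.8775, and 0.85·0.75 + 0.15·3.3 = 1.1325. Difference: 0.255.
- Mean squared grades are 1.35 (non-serious) and 11.1 (serious), so the arm variances are 1.0675 and 1.5299.
- SE under the null = √(2·(1.2987 + 0.255²/4)/110) = 0.1546. SE under the alternative = √(2.5974/110) = 0.1537.
- Power ≈ Φ((0.255 − 1.96·0.1546)/0.1537) = Φ(−0.31) ≈ 0.38, which agrees with the simulated 38%.

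| Serious events, placebo vs drug | Mantel on all events, A | Mantel on all events, B | Fisher test on serious-event incidence |
|---|---|---|---|
| 5% vs 10% | 16% | 14% | 21% |
| 5% vs 15% | 45% | 38% | 64% |
| 10% vs 20% | not run | 33% | 48% |

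The A column counts only results against the drug, and B counts both directions. The difference is negligible when the drug has the excess.

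**4. What an interval would show.** The half-width of a 95% interval for the risk difference is 1.96·√((p₀(1−p₀) + p₁(1−p₁))/110). At 5% in both arms it is 5.8 percentage points. At 5% versus 10% it is 6.9, giving −1.9 to 11.9. At 5% versus 15% it is 7.8, giving 2.2 to 17.8. The interval shows what excess the trial can and cannot rule out. A p-value on non-serious grades does not.

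**The case against.** A reader might infer that serious harm goes unexamined. The documents do not support that. Serious events are described, and the sentence in Safety outcomes on counts and rates by study group naturally includes them, so an excess would be visible.

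A reader might also infer that safety will be declared from a non-significant Mantel result. Nothing says so: the only criterion for calling the drug useful is superiority on an efficacy endpoint. Nor is all severe harm excluded, since non-serious events of grade 3 or higher stay in the test.

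One can construct a case in which the test as written favours the drug because severe non-serious events become serious ones. It requires non-serious grade 3 events to fall from 10% to 2% while serious events rise from 5% to 15%, and nothing in the article suggests such a pattern.

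Three further points have force. Describing serious events without a test is ordinary in a 220-patient trial sized for efficacy. Power would be low even with them included: a Fisher test at 1.3% versus 5% has about 19%. And *other* may be loose wording in a condensed article.

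All this limits the size of the point. It does not remove it, because the article chose a test and fixed its scope, and that scope drops serious events from a quantity called the highest grade. The low-power argument favours reporting an interval.

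**Conclusion.** The point holds, as a minor one. As written, the only named between-arm safety comparison leaves serious events out of each subject's highest grade and is uninformative about an excess of them. Serious events remain described and, on the natural reading, counted by arm; what is lacking is a formal comparison or an interval.

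The conclusion on scope rests only on reading *other* as non-serious. The power figures rest on assumed serious-event rates, assumed grade distributions and an assumed two-sided 5% level, and they illustrate rather than measure the loss. The 1.3% quoted in Background is for adverse drug reactions of any kind and cannot stand in for a serious-event rate. No efficacy figure, primary analysis or decision rule is affected.

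**What to change.** In Statistical analysis, delete *other*, so that the highest CTCAE grade is taken over all adverse events, serious and non-serious, before the Mantel test. Add the incidence of at least one serious adverse event by arm in the safety analysis set, with the risk difference and its 95% confidence interval. Keep the serious-event narratives. If the full protocol already grades all events, only the wording needs aligning.

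The cost is one edited sentence and one extra table, with no new data or patients. The downside is that the severity comparison may look less favourable to the drug.

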### Quality control and assurance

The study-related division of the sponsor, Tsumura & Co., performs quality control. Clinical research associates decide on issues related to data entered into the electronic data capture system and report their conclusions to the investigator. If any problems are anticipated, the investigator takes the appropriate measures.

To determine whether the study is being conducted in accordance with the protocol and the GCP, the GCP audit division of the sponsor performs a GCP audit and formulates an appropriate plan following the Tsumura-GCP audit procedure.

The GCP audit division of the sponsor performs GCP audits of all facilities involved in this study, including the study site and facilities at external organizations and contract research organizations, at appropriate times during or after the study.

### Research ethics approval

This study was designed and is undertaken in compliance with the Declaration of Helsinki and the “Ethical Guidelines for Medical and Health Research Involving Human Subjects” (Public Notice of the Ministry of Education, Culture, Sports, Science and Technology and the Ministry of Health, Labor and Welfare). All study protocols, informed consent forms, and other requested documents were approved by the Institutional Review Board and the Ethics Committee of the National Cancer Center in Japan.

The investigators sufficiently explain the details of the study to the subjects in accordance with the informed consent documents and obtain subjects’ voluntary written consent to participate in the study. After provision of consent, subjects are withdrawn from the study according to the following criteria: (1) if the subject withdraws consent; (2) if the primary disease is exacerbated or an adverse event occurs, and continuation of the study is judged to be difficult; (3) if a subject is found to be ineligible for the study after it begins; and (4) if a subject discontinues the study treatment at his or her own discretion.

The documents or records that should be stored at the study site, including those related to subject consent, those on which case report forms are based, records of deliberation by the review board, documents related to requests and contracts for the study, and the management table for study drugs, will be stored for 3 years after the discontinuation or completion of the study. After the storage period, the documents and records will be anonymized and discarded by an appropriate method. We do not plan to grant public access to the full protocol, participant-level dataset, or statistical code.

## Discussion

Preoperative anxiety and postoperative delirium affect both short- and long-term prognoses in patients with cancer and therefore need to be appropriately assessed, treated, and prevented. However, neither preventive nor therapeutic methods have been established for these conditions.

The present study is the first randomized, double-blind, placebo-controlled study conducted to clarify the effects of a Japanese herbal medicine, Yokukansan, for the prevention and treatment of perioperative psychiatric symptoms in patients with cancer. Although Yokukansan has already been approved for anxiety, existing findings are insufficient to allow a clear conclusion regarding its efficacy in preoperative conditions in particular. There are no standard therapeutic regimens for preoperative anxiety or postoperative delirium in cancer patients. For these reasons, if the present study can clarify the therapeutic effect of Yokukansan on preoperative anxiety, its preventive effect on postoperative delirium, and its safety in cancer patients, it will greatly contribute to the establishment of standard therapies for perioperative psychiatric symptoms in this population, leading to the provision of safer medical care with higher compliance. However, if the effect of Yokukansan is not verified in this study, the lack of clear evidence will suggest that continued use of this agent in daily practice can be stopped.

## Trial status

The protocol version number is Ver 3.2, and the date is September 6, 2017. The trial was initiated on August 14, 2017, with 195 subjects randomized by October 5, 2018. We plan to complete recruitment on March 31, 2019.

## Abbreviations

ᅟPSD: Behavioral and psychological symptoms of dementia
CTCAE v 4.0: Common Terminology Criteria for Adverse Events, fourth version
DRS-R-98: Delirium Rating Scale-Revised-98
DSM-5: Diagnostic and Statistical Manual of Mental Disorders, Fifth Edition
GCP: Good Clinical Practice
HADS-A: Hospital Anxiety and Depression Scale-Anxiety
HADS-D: Hospital Anxiety and Depression Scale-Depression
J-SUPPORT: Japan Supportive, Palliative and Psychosocial Oncology Group
